#### Adherence of participants

Due to the self-guided IMI format, the IMI content as well as the simulated personalization, are highly standardized across participants. To enhance participants' engagement with the intervention, they will receive a push-up notification whenever a new session or assessment is available to them. Other adherence-fostering measures include standardized automatic feedback messages after completion of every module. Adherence to the assessments will additionally be supported through monetary incentives (see Section “Plans to promote participant retention and complete follow-up {18b}”). Adherence will be monitored through the DIRECT platform, which automatically records participants' engagement with the IMI (e.g., start or completion of a session, the amount of time spent in a session, and the frequency of exercise access).

### Relevant concomitant care permitted or prohibited during the trial {11d}

Participants will be considered eligible if they enter the trial with no or stable antidepressant regimen, defined as no changes in substance or dosage for at least four weeks. Participants using benzodiazepines will be excluded because of their acute effects on depressive symptoms (e.g., mood and sleep) which may influence participants’ self-report. Concurrent psychotherapy is also not permitted (see “Eligibility criteria {10}”). To avoid the between-group comparisons being confounded by starting a new or changing an ongoing treatment, we will discard the data of participants who indicate that they (i) started a psychotherapy or pharmacological treatment or (ii) changed the dosage or agent during the trial. We will model the missing observations in a manner that mimics a scenario in which this treatment uptake/change did not occur.

### Provisions for post-trial care {30}

N/a: There is no ancillary post-trial care or compensation.

### Outcomes {12}

#### Primary outcome

The primary outcome measure is depression, as assessed by the Beck Depression Inventory-II (BDI-II) [23, 24]. Change from baseline is used to describe within-group symptom change. In our main analysis which targets the difference between the treatment arms/factor levels, we consider the mean difference in BDI-II scores at the corresponding measurement occasions (3, 6, and 12 weeks after randomization) as relevant endpoints. The BDI-II is a 21-item self-report questionnaire assessing the severity of depressive symptoms over the past two weeks. Total scores range from 0 to 63. Higher scores indicate more severe depressive symptoms, with established cut-off points for minimal (0–13), mild (14–19), moderate (20–28), and severe depression (29–63). The BDI-II has demonstrated satisfactory psychometric properties, including high internal consistency and test–retest reliability, making it one of the most widely used outcome measures in psychotherapy research.

#### Secondary outcomes

All secondary outcome measures (see Table 2) have shown satisfactory reliability and validity in previous studies. In addition to the BDI-II, depression will be assessed with the 9-item Patient Health Questionnaire (PHQ-9) [25, 26]. Functioning will be assessed with the German version of the 5-item Work and Social Adjustment Scale (WSAS) [27, 28]. We will determine disability with the 7-item Pain Disability Index (PDI) [29, 30]. For sex-specific symptoms, we will assess menopausal symptoms using the Menopause Rating Scale (MRS) [31, 32]. Additionally, we will assess gender-sensitive depressive symptoms with the 25-item Gender-Sensitive Depression Screening (GSDS-25) [33]. The sex-specific symptoms will only be assessed for participants that identified with the respective sex. Personality will be assessed using the short 10-item version of the Big Five Inventory (BFI-10) [34]. We will assess satisfaction with treatment with an adapted version of the 8-item Client Satisfaction Questionnaire (CSQ-8) for IMIs [35, 36] and usability with a newly developed short scale (RAD Usability Scale). We will also ask participants to rate their goal attainment post-treatment for up to three goals they have set for themselves in module 2 of the IMI. Negative effects will be measured with the 25-item Inventory for the balanced assessment of Negative Effects of Online Interventions (INEP-ON) [37].

**Table 2 Tab2:** Schedule of enrollment, interventions, and assessments

	**Study period**										
	**Enrollment**	**Baseline**	**Allocation**	**Post-allocation**							
**Timepoint****	*−t*_*1*_	*t*_*0*_	**0**	*Week 1 (t*_1_**)**	*Week 2 (t*_*2*_**)**	*Week 3 (t*_*3*_*)*	*Week 4 (t*_*4*_*)*	*Week 5 (t*_*5*_*)*	*Week 6 (t*_*6*_*)*	*Week 12 (t*_*7*_*)*	*Other*
Enrollment:											
Eligibility screen	X										
Informed consent	X										
Allocation			X								
Interventions:											
Simulated Personalization				X							
Personal Contact						X					
IMI modules				X	X	X	X	X	X		
Assessments:											
Sociodemographics	X	X									
Anxiety and Depression State and Trait (STADI)		X							X		
Expectations (TEX-Q)		X									
Subjective Stress (PSS-10)		X									
Somatosensory Amplification (SSAS)		X									
Desire for Relief (self-drafted)		X									
Acceptance (UTAUT)		X									
Depression (BDI-II)	X					X			X	X	
Depression (PHQ-9)		X		X	X	X	X	X	X	X	
Functioning (WSAS)		X							X		
Disability (PDI)		X							X		
Menopausal Symptoms (MRS)		X							X	X	
Depression gender-sensitive (GSDS)		X							X		
Personality (BFI-10)		X									
Goal Attainment (GAS)									X		
Negative Effects (INEP-ON)									X		
Usability (RAD									X		
Satisfaction with Treatment (CSQ-8)									X		
Expectations (GEEE)		X		X	X	X	X	X	X		
Prior Experiences (GEEE)		X									
Treatment Effects (GEEE)									X	X	
Session Fit (self-drafted)				X	X	X	X	X	X		
Self-Efficacy (ASKU)				X	X	X	X	X	X		
Working Alliance (WAI-I)				X	X	X	X	X	X		
Subjective Adherence (self-drafted)				X	X	X	X	X	X		
Warmth & Competence of Telephone Contact (SCM)											X
Warmth & Competence of App (SCM)						X			X		

The sociodemographic variables include age, sex and gender, education, employment status, relationship status, sexual orientation, ethnicity, body measurements (height, weight, handedness), religion, disability, menstruation, and menopausal status. *ASKU*, Allgemeine Selbstwirksamkeit Kurzskala (general self-efficacy short scale); *BDI-II*, Beck Depression Inventory-II; *BFI-10*, Big Five Inventory-10; *CSQ-8*, Client Satisfaction Questionnaire-8 adapted to the IMI context; GAS, Goal Attainment; *GEEE*, Generic Assessment of Expectancies and Experiences; *GSDS*, Gender-Sensitive Depression Scale; *INEP-ON*, Inventory for the balanced assessment of Negative Effects of Psychotherapy - Online Intervention version; *MRS*, Menopause Rating Scale; *PDI*, Pain Disability Index; *PHQ-9*, Patient Health Questionnaire-9; *PSS-10*, Perceived Stress Scale-10; *SSAS*, Somatosensory Amplification Scale; *STADI*, State-Trait Anxiety-Depression Inventory; *TEX-Q*, Treatment Expectancy Questionnaire; *UTAUT*, Unified Theory of Acceptance and Use of Technology; *SCM*, Warmth and competence scales from the Stereotype Content Model; *WAI-I*, Working Alliance Inventory for Online Interventions-Short Form; *WSAS*, Work and Social Adjustment Scale; *Self-drafted*, Custom questionnaire developed for the study or CRC 289

#### Predictors

The sociodemographic variables include age, sex and gender, education, employment status, relationship status, sexual orientation, ethnicity, religion, and disability and were adapted from Ballering et al. [38] as well as Stadler et al. [39]. Additionally, we will assess body measurements (height, weight, handedness) as well as menstruation and menopausal status. Predictors include prior psychotherapy experience and the use of IMIs, assessed via the Generic Rating Scale for Previous Treatment Experiences, Outcome Expectations, and Treatment Effects (GEEE) [40]. Expectations will furthermore be assessed using the Treatment Expectation Questionnaire (TEX-Q) [41, 42]. Attitudes toward bodily sensations will be measured using the Somatosensory Amplification Scale (SSAS) [43, 44]. Anxiety and depression state and trait characteristics will be assessed using the State-Trait Anxiety-Depression Inventory (STADI) [45]. Subjective stress, including aspects of hopelessness and self-efficacy, will be measured using the 10-item Perceived Stress Scale (PSS-10) [46, 47]. To evaluate technology acceptance, we will apply the Unified Theory of Acceptance and Use of Technology (UTAUT) [48, 49]. Additionally, we will assess one item measuring the desire for relief, which was developed as part of CRC 289.

#### Psychotherapy mechanism-related constructs

We will measure expectations** (**GEEE) [40], self-efficacy [50], therapeutic alliance [51, 52], subjective adherence (translated and adapted from the item used by Smoktunowicz et al. [53]) as well as the perceived fit to this week's online module (self-drafted item) weekly. Warmth and competence of the IMI will be measured mid- and post-treatment using an adapted version of the warmth and competence scales from the Stereotype Content Model [12]. The warmth and competence of the telephone counselor will be measured following the telephone call.

#### Qualitative interviews

Twenty strategically and sequentially selected patients will also be answering questions in an in-depth semi-structured qualitative telephone interview about their experience and perceived mechanisms of change of treatment post-treatment. In selecting participants, we strive for a balance of treatment groups and gender.

### Participant timeline {13}

Figure 1 depicts the CONSORT flowchart.

**Fig. 1 Fig1:**
[figure not shown]
CONSORT flow diagram

### Sample size {14}

To depict a clinically meaningful effect size of *d* = 0.35 between two arbitrary cells (e.g., personalized framing and expectation-optimizing contact vs. standard framing and no contact) in this proof-of-concept study, with an alpha of 0.05 and power of 0.80 (one-tailed, uncontrolled for multiplicity), an overall sample size of approximately 200 is needed according to G*Power [14]. The resulting sample of *N* = 600 (*n* = 100 per cell) should be sufficiently large to depict trends and inform future confirmatory trials. To consider a dropout rate of 20% per arm, we aim to recruit *N* = 720 patients (120 per treatment arm). We will include data assessed before starting the intervention as covariates to increase power.

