**Methods:**

All participants will receive an established IMI consisting of six evidence-based cognitive behavioral modules. In this 2×3 factorial design, 720 adult participants will be randomized to receive (1) either the IMI in standard or personalized framing (first randomization factor), in combination with (2) an expectation-focused telephone call mid-treatment, a supportive phone call or no phone call (second randomization factor). The primary outcome is depression at mid- and post-treatment (BDI-II). Secondary measures include expectations, adherence, state and trait anxiety and depression, disability, negative effects, and satisfaction with treatment.

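### The recruitment target of 720 adds 20% to 600 instead of dividing by 0.80, so the stated 20% dropout leaves 576 (96 per cell), not 600 (100 per cell).

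*Protocol article*

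**What the plan says.** All the figures stand in the Sample size {14} section of the protocol article.

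- Effect and comparison: "To depict a clinically meaningful effect size of *d* = 0.35 between two arbitrary cells".
- Error rates: "with an alpha of 0.05 and power of 0.80 (one-tailed, uncontrolled for multiplicity").
- Result for one two-cell comparison: "an overall sample size of approximately 200 is needed according to G*Power".
- Scaled to six cells: "The resulting sample of *N* = 600 (*n* = 100 per cell) should be sufficiently large to depict trends".
- Allowance for losses: "To consider a dropout rate of 20% per arm, we aim to recruit" 720 patients, that is "120 per treatment arm".

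The Abstract repeats the target as the number to be randomized: "720 adult participants will be randomized". The Trial design {8} section confirms six arms with equal allocation. No other section gives a different dropout rate or a different expected number of completers.

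**The concern.** The section states three quantities: 100 per cell retained, 20% dropout per arm, and 120 per arm recruited. Any two of them fix the third, and the three given do not agree. If dropout turns out exactly as assumed, the trial will still finish below the size on which its power statement rests.

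The margin matters a little more because dropout is not the only planned loss of outcome data. Under Relevant concomitant care {11d} and the missing-data section {20c}, measurements are to be discarded for participants who start psychotherapy, or who start or change medication, during the trial. The sample size section makes no separate allowance for this.

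**Working it through.** **Inputs, all from Sample size {14}.** d = 0.35; one-tailed alpha 0.05; power 0.80; no multiplicity adjustment; 100 per cell over six cells (600); dropout 20% per arm; target 120 per arm (720).

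**Step 1. Reproduce the two-cell figure.** For a two-sample t test with n per cell, df = 2n − 2 and the noncentrality parameter is d × √(n/2). The smallest n with one-tailed power of at least 0.80 is 102 per cell, 204 in total (power 0.801). The normal approximation gives 101 per cell. Both agree with the stated figure of about 200. A two-tailed test would need 130 per cell, so the one-tailed reading is the one used. Then 6 × 100 = 600.

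**Step 2. Reproduce the recruitment target.** Two ways of allowing for dropout q = 0.20:

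| Formula | Per arm | Total |
|---|---|---|
| n × (1 + q) | 100 × 1.20 = 120 | 600 × 1.20 = 720 |
| n / (1 − q) | 100 / 0.80 = 125 | 600 / 0.80 = 750 |

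The first row gives the plan's figure exactly. Only the second row leaves the required number, because dropout is a fraction of those randomized, not of those retained.

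**Step 3. What 720 delivers.**

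- Retained per cell: 120 × 0.80 = 96.
- Retained overall: 720 × 0.80 = 576.
- Shortfall: 600 − 576 = 24, or 4 per cell (4%).
- Dropout at which 720 still leaves 600: 1 − 600/720 = 16.7%.

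**Step 4. Effect on power for the stated test** (noncentral t, one-tailed alpha 0.05).

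| n per cell | Power at d = 0.35 | d detectable with power 0.80 |
|---|---|---|
| 102 | 0.801 | – |
| 100 | 0.794 | 0.353 |
| 96 | 0.780 | 0.360 |

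The dropout step costs 0.7943 − 0.7798 = 0.0145, about 1.5 percentage points. A further 0.7 points (0.801 to 0.794) come from rounding 204 down to 200, so there was no slack to absorb the slip. Carrying the unrounded 102 through would give 102/0.80 = 127.5, that is 128 per arm and 768 in total.

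**The case against.** The arithmetic is not in dispute. The case on the other side is that it hardly matters.

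- **Covariates.** The same section plans baseline covariates to raise power, and the analysis is an ANCOVA with age and baseline severity. The G*Power figure is for an unadjusted comparison. Taking effective n as roughly n/(1 − r²), 96 per cell is worth 102 once r² reaches 1 − 96/102 = 0.059, a covariate–outcome correlation of about 0.24. The protocol gives no r, so this is an assumption: r = 0.2 gives an effective 100 per cell, r = 0.3 about 105, r = 0.5 128. This point stands. A modest correlation would cover the whole loss.
- **Multiple imputation.** The main analysis imputes missing outcomes for all randomized participants, supported by within-treatment covariates, and the PHQ-9 is collected weekly. It is not a completer analysis of 576, so 96 per cell is a conservative figure for the information lost to dropout. This stands in part: imputation recovers only what the observed data predict, and the plan does not say how much. The sample size section itself counts completers, since it inflates for dropout.
- **Larger contrasts.** The two-cell comparison is the smallest in the design. With 96 per cell, the framing comparison has 3 × 96 = 288 per side and each pair of contact levels 2 × 96 = 192 per side. This is correct, but the stated power refers to two cells.
- **Approximate, proof-of-concept sizing.** The word for approximation is attached to the 200. The 600, the 100 per cell, the 20% and the 120 per arm are stated without it.

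These points limit the consequence. None of them was used to derive 720, and none makes the three stated figures agree.

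**Conclusion.** The point holds. With the stated 20% dropout, 720 randomized leaves 576 (96 per cell), not 600 (100 per cell); 720 is consistent only with 16.7% dropout. The shortfall is 24 participants with observed outcomes, and power for the stated test falls from 0.794 to 0.780. The power figures assume a two-sample t test of two cells, one-tailed alpha 0.05, d = 0.35, no covariates and completers only. Under the planned ANCOVA with imputation the real loss is probably smaller and may be nil, but the document gives no figure from which to show this. The validity of the trial is not affected and more participants are not required. A stated sample-size figure is wrong and should be corrected.

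**What to change.** Keep 720 and correct the sentence in Sample size {14}. For example: with 720 randomized (120 per arm) and 20% dropout, about 576 participants (96 per cell) are expected to provide outcome data, which gives power of about 0.78 for d = 0.35 in an unadjusted one-tailed comparison of two cells; covariate adjustment is expected to raise this. If the team wants to claim the gain from covariates, it should state the correlation assumed.

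Two other wordings are also consistent. One is to recruit 750 (125 per arm), which keeps both the 20% and the 100 per cell at the price of 30 more participants. The other is to state that 720 allows for 16.7% dropout, but this changes a planning assumption to fit the target and should be used only if the team has grounds for the lower rate.

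The first option costs one sentence and a slightly less favourable power figure. Recruitment is expected to run to mid-2027, and an updated statistical analysis plan is promised before the main analysis, so the correction can be made there and noted as a correction to the published protocol.

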### Recruitment {15}

Participants will be recruited through several recruitment channels. We will distribute information about the study through social media posts on an Instagram page created for this study. Selected posts will also be advertised. We will also share postings on other social media platforms as well as online discussion forums focused on mental health. It is also planned to collaborate with patient advocacy networks to increase the study's visibility. We will also cooperate with the other CRC sites to advertise the study. From all these channels, interested parties will be directed to a study website where they can learn more about the study and find instructions to download the DIRECT app.

## Assignment of interventions: allocation

### Sequence generation {16a}

An independent researcher not involved in the study team will generate a permuted block randomization list with varying block sizes using the sealed envelope web app [54].

### Concealment mechanism {16b}

The independent researcher who generated the allocation sequence will share this list with the DIRECT app developers who implement the randomization list into the intervention system. The implementation of the allocation sequence into the platform ensures that the allocation sequence is always concealed and cannot be changed by the study team.

### Implementation {16c}

Participants are self-selected, meaning they enroll themselves in the trial. Once they are considered eligible to participate (i.e., after the online eligibility screening), a member of the study team will allocate participants to one of the six groups by pushing a button in the DIRECT admin panel. The platform automatically assigns the participant to the group that is next in line based on the concealed block-randomized list stored on the platform.

## Assignment of interventions: blinding

### Who will be blinded {17a}

Due to the nature of psychotherapeutic treatment trials, full blinding is not possible. Participants will be informed that they are receiving a specific version of a digital intervention. However, they will be blind concerning the differences between the specific study groups. As study personnel delivering the mid-treatment intervention delivery (e.g., telephone call) must know the allocation to deliver the correct intervention, blinding them is not possible.

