#### Personalization expectation

With the first randomization factor (2 levels), we aim to modulate expectations by simulating a personalized IMI. Participants in the “personalized” arm will receive a sham version of the IMI that they believe is tailored to their needs based on their baseline data (although it is the same intervention as in the comparison group). Specifically, participants will be informed that the study team has selected the most suitable intervention components for them. The following measures will be taken to make the simulated personalization salient:Before initiating the first module, participants are informed about the group to which they were randomized. Participants in the personalized group are informed about a personalized selection of the intervention modules based on their previously entered data, as well as the concept and expected benefits of personalized interventions. Participants in the standard group will receive an informative text about receiving the intervention in a previously established version. All of this information is conveyed written in the app.In addition to informing them about their group allocation and the personalized modules, we introduce the metaphor of a “key-lock-principle.” The standard group will receive no further specification through means of a metaphor.For the personalized group, the picture of a key will be displayed visually along with the CBT exercises in each of the six modules to make the “key-lock-principle” salient. In the standard group, we will display a generic picture of a thought bubble (see 4. below).Within each module, we will tailor the headline of the psychoeducation of the respective exercise to the allocated group. While it will read “Why am I doing this?” in the standard group, the personalized group will read the headline “Why was this selected for me?”. The provided informative text about the relevance of the exercise will be the same for both groups.Finally, after each module, we will assess how participants perceived the fit of the session to their needs (“session fit”). Thus, we expect to increase participants’ perception that the intervention is indeed personalized by creating the impression of asking about the efficacy of an underlying matching procedure. For the standard group, we will ask the same question. Since we did not introduce an adaption for this group, we expect that group to perceive the question about the “session fit” as a routine form of evaluation.

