#### Personal contact mid-treatment

With the second randomization factor, we will investigate the effects of different variants of personal contact mid-treatment. Participants will either receive (1) no personal contact via telephone or a phone contact that is (2) supportive without focusing on expectations or (3) expectation-optimizing. The (2) non-specific telephone calls are exclusively supportive, without touching upon expectations. Thus, the supportive contact will not have a specific topic. Instead, participants are free to share any topic or concern. The telephone counselors will be trained to respond in a non-directive, empathetic manner. However, they are instructed to avoid any interventions, including interventions that may target expectations. In the (3) expectation-optimizing contact, the phone contact will focus on the expectations of the participants. The participants will be asked about their previous experiences with the intervention and about what they expect to change until the end of the intervention. The phone counselors will be trained to analyze participant’s expectations, enhance positive and realistic expectations, and modify maladaptive or unrealistic expectations by using interventions that are useful in optimizing expectations [20], including psychoeducation, informing about the effectiveness of the interventions, or increasing participants’ sense of control, in a warm and competent manner. The non-content-related aspects of the personal contact in conditions (2) and (3) are parallelized between the arms. The duration of the telephone contacts are planned to be 20 to 30 min. Counselors are master students of clinical psychology/psychotherapy who demonstrate psychotherapeutic relationship skills (e.g., empathic listening, validation). They will receive comprehensive training before treating the first client (see Section “Strategies to improve adherence to interventions {11c}”) to ensure that the intervention is delivered in a consistent manner across all participants.

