### Strategies to improve adherence to interventions {11c}

#### Adherence of telephone counselors

To enhance comparability and ensure adherence to the intervention protocol and the delivery of the personal contact intervention, we have implemented several measures: (1) each telephone counselor will be trained to conduct either the expectation-optimizing or non-specific, supportive telephone calls, (2) all counselors receive a talk schedule, (3) the first 2 (more if necessary) telephone calls conducted by each counselor will be carried out jointly with the supervisor. Moreover, (4) the next 2–3 conducted calls will be rated for fidelity by an external observer. In case of insufficient fidelity, telephone counselors will receive additional, targeted training as determined on a case-by-case basis by the supervisor. (5) After this training period, telephone counselors will conduct calls independently under weekly supervision. A psychotherapist with extensive expertise in IMIs will train and supervise counselors.

During the intervention phase, 10–20% of phone calls will be audio-recorded and evaluated for fidelity to the core principles by an external observer.

For the fidelity ratings, a study-specific measure was developed based on established fidelity scales [21, 22] and adapted to the specific requirements of the telephone calls in this study. Participants receiving the contact mid-treatment will also be asked, after the phone call, to indicate in one open-ended question what the contact was about. Telephone counselors will also rate how they adhered to the talk schedule.

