### Procedure for unblinding if needed {17b}

There is no blinding of study personnel, so unblinding is not necessary. After the “last patient in” completes the study, we will debrief participants in the simulated personalization group that they did not receive a personalized treatment.

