## Discussion

This RCT investigates whether expectation-focused micro-interventions can improve the effects of an IMI for adults with self-reported symptoms of depression. While in other contexts, expectation-focused interventions have been shown to improve outcomes [57], this has yet to be explored in IMIs. The goals of this study are threefold.

First, we aim to investigate the effects of tapping into expectations around personalization. Personalization is considered a way to improve treatment effects [58]. We have recently conducted a systematic review on personalization in IMIs and found generally weak evidence of the superiority of personalized over standard IMI components. Findings revealed that the implementation and communication of personalization were insufficiently detailed. This study aims to fill this gap by uncovering the underlying mechanisms behind personalization. If our study reveals that framing the IMI as personalized is sufficient to yield decreases in depressive symptoms, it could have significant clinical implications. More emphasis may be given on how to communicate treatments to patients. Future studies should then investigate whether enhanced effects in personalized treatments arise from an actual match between patients and IMI components or from expectation effects (i.e., "a treatment that is personalized to me must help me more").

Second, we aim to investigate if personal contact provided ~3 weeks after treatment initiation optimizes outcome expectations and depressive symptoms. Human support is considered important in IMIs [59]. Comparing a group with no human contact to groups that receive either expectation-focused or non-focused contact allows us to examine whether it is human contact per se or the specific expectation-optimizing strategies that optimize outcome expectations and decrease depression. Instead of more static, text-based guidance, synchronous telephone contact allows for optimizing the expectations in a personalized manner, as different levels of expectations—low, realistic, and overly optimistic expectations—and concerns may require the use of different psychotherapeutic techniques.

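### The stated reason for not blinding telephone counselors covers call type only; as written, the plan also leaves them free to know the framing arm, which could bias the framing contrast and the framing-by-call interaction at weeks 6 and 12

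*Protocol article*

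**What the plan says.** Section {17a} gives one reason for leaving the staff who make the calls unblinded: they "must know the allocation to deliver the correct intervention, blinding them is not possible". Section {17b} is broader: "There is no blinding of study personnel, so unblinding is not necessary". Neither separates the two randomization factors.

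Four other places show what the allocation contains and what a call requires:

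- Under Implementation {16c}, "a member of the study team will allocate participants to one of the six groups by pushing a button in the DIRECT admin panel". The allocation is one of six cells, so it carries framing as well as call type.
- Under Personalization expectation, of the text that sets up the framing: "All of this information is conveyed written in the app".
- Under Adherence of telephone counselors, "each telephone counselor will be trained to conduct either the expectation-optimizing or non-specific, supportive telephone calls".
- Under Personal contact mid-treatment, the expectation call is described thus: "The participants will be asked about their previous experiences with the intervention and about what they expect to change until the end of the intervention". Counselors are trained, among other tasks, to "modify maladaptive or unrealistic expectations by using interventions that are useful in optimizing expectations". Nothing in that section varies with framing.

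The Discussion places the call in time: "personal contact provided ~3 weeks after treatment initiation". The week 6 and week 12 outcomes follow it.

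**The concern.** F1 is itself an expectation manipulation, and the telephone call is the one point in the trial where a person discusses expectations with the participant. A counselor who knows that a participant's personalization is simulated could treat the resulting optimism as unrealistic and correct it, or could protect the cover story and reinforce it. Either way, what happens in the call would depend on F1 through the counselor's knowledge and not only through what the participant brings.

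This would matter for the estimates that follow the call. Section {20a} puts the F1×F2 interaction in the week 6 and week 12 models and promises marginal means for each level of both main factors. The Strengths and limitations section presents separation of independent and interactive effects as an advantage of the factorial design. If counselors acted on F1, those contrasts would mix framing with counselor behavior.

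**Working it through.** **Step 1: does a call require knowledge of F1?**

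| Element | Where stated | Needs F1? | Needs F2? |
|---|---|---|---|
| Delivering the framing | Personalization expectation: done in the app | Not a counselor task | No |
| Content of the supportive call | Personal contact mid-treatment: open topic, no interventions | No | Yes |
| Content of the expectation call | Same section: experiences, expectations, psychoeducation | No | Yes |
| Assigning a counselor | {11c}: trained in one call type | No | Yes |

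A counselor with a list of people to call can do the task. The reason in {17a} supports openness to F2 and says nothing for openness to F1.

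**Step 2: how would a behavior difference carry into the contrasts?**

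The documents give no size, so let b be an assumed net shift in BDI-II, in SD units, in a personalized call cell because the counselor knows F1. The no-contact cells have no call and shift by 0. Write b_S for the supportive call and b_E for the expectation call.

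- Shift in the marginal F1 effect = (0 + b_S + b_E)/3
- Shift in F1 × (expectation vs no call) = b_E
- Shift in F1 × (supportive vs no call) = b_S
- Shift in F1 × (expectation vs supportive) = b_E − b_S

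| Assumed b | F1, expectation call only (b/3) | F1, both calls (2b/3) | Interaction, affected call vs no call |
|---|---|---|---|
| 0.05 | 0.017 | 0.033 | 0.05 |
| 0.10 | 0.033 | 0.067 | 0.10 |
| 0.20 | 0.067 | 0.133 | 0.20 |

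In the expectation-versus-supportive interaction the shift is b if only the expectation call is affected, and 0 if both calls shift equally.

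**Step 3: how large is that against the trial's precision?**

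The plan's cell size reproduces. For d = 0.35, one-tailed alpha 0.05 and power 0.80, 2 × (1.645 + 0.842)² / 0.35² gives 101 per cell, 202 for two cells (204 with the t distribution), against about 200 stated. The blinding point does not rest on this figure; it only supplies n = 100 per cell.

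With SD = 1, n = 100 per cell and no gain from covariates:

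- SE of the marginal F1 effect (300 vs 300) = √(2/300) = 0.082
- SE of one interaction contrast (four cells) = √(4/100) = 0.200

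If the true effect were zero and b acted in one consistent direction, the two-sided error rate at nominal 0.05 would be:

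| Assumed b | F1, both calls affected | One interaction contrast |
|---|---|---|
| 0.05 | about 0.07 | about 0.06 |
| 0.10 | about 0.13 | about 0.08 |
| 0.20 | about 0.37 | about 0.17 |

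If only the expectation call is affected, the F1 shift is half as large: b = 0.10 then gives about 0.07, and b = 0.20 about 0.13.

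**Step 4: who is in the affected cells?**

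At 120 per arm, the personalized call cells hold 2 × 120 = 240 of 720 participants, or 120 if only the expectation call matters. These are upper bounds, since {11b} provides written material in the app when a call is not completed.

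**The case against.** The strongest reply is that no passage says counselors are shown F1. In {17a} the allocation can be read as call type alone, and what each admin-panel role displays is operational detail that an article may leave out. This stands as a limit on the claim: exposure is permitted by the text, not documented. It does not remove the point, because {17b} states without qualification that study personnel are not blinded.

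Several further points also stand:

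- Judging and changing expectations is the task of the expectation call. Supportive counselors are told to avoid interventions, including any aimed at expectations. The b/3 case therefore fits the mechanism better than 2b/3.
- The expectation call is meant to respond to the expectations a participant voices, including those that framing created. That is part of the interaction under study. Only the extra effect of the counselor's own knowledge is bias.
- Outcomes are self-reported in the app, so the route is behavior in the call and not outcome rating.
- Talk schedules, joint first calls, weekly supervision and fidelity rating of 10–20% of calls limit drift, although none is described as hiding framing.
- Expectations at week 1 (sub-question 2) precede any call, and the week 3 F1 comparison is largely unaffected.
- Participants may disclose their framing in the call, so masking narrows the route without closing it.

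A reader might also infer that external fidelity raters and the staff who answer messages know F1. The documents do not say what either group sees.

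**Conclusion.** The point holds as a gap between reason and conclusion. The justification in {17a} supports openness to call type only, yet {17a} and {17b} together leave counselors free to know framing. That opens an avoidable route to bias in the F1 contrast and the F1×F2 interaction at weeks 6 and 12.

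Size and direction are unknown. The 0.05–0.20 SD range is an assumption with no support in the documents, and correcting and reinforcing behaviors could partly cancel. What follows by arithmetic is the pattern: b/3 or 2b/3 in the marginal F1 effect, b in the interaction of an affected call against no call, and nothing in the expectation-versus-supportive interaction if both calls shift equally.

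Two stronger readings are not supported. A reader might conclude that the framing estimates are biased; the documents show only that the plan allows it. A reader might also express the shift as a share of d = 0.35; in {14} that figure is a difference between two cells, not a marginal F1 effect, so the ratio would compare different contrasts.

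**What to change.** - In {17a}, limit the statement to call type: counselors know which call they deliver and remain masked to framing.
- Give counselors call lists and an admin-panel view without the F1 field.
- Add the same neutral response to both talk schedules for when a participant raises the selection of modules.
- Have counselors record after each call whether framing was disclosed.
- Correct {17b} so that it no longer says that no personnel are blinded.

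Extending the masking to fidelity raters and message staff is optional.

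The cost is a view setting, a line in each talk schedule, one record item and a change of wording. The Confidentiality section {27} already describes differing roles within the study team. No arm or sample size changes. The downside is that masking will be partial. Recruitment is expected to run to mid-2027, so later calls could still benefit. If counselors are already masked to F1 in practice, only the wording of {17a} and {17b} needs correcting on the masking itself.
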